Preparedness programs at both community and individual levels remain limited globally. Moreover, existing initiatives tend to focus on raising awareness of diseases and natural disasters rather than implementing operational strategies to address outbreaks and emerging threats [4,7]. In Malaysia, community preparedness efforts are largely centered on flood disasters, with limited engagement of indigenous populations [9]. Existing programs primarily aim to raise awareness and reduce disease transmission risks; however, evidence suggests that such approaches do not necessarily translate into tangible preparedness outcomes [10,11]. To achieve preparedness, individuals should possess cognitive aspects of preparedness, including knowledge and positive attitudes, and should also demonstrate these through tangible behavior [12,13]. Preparedness programs should therefore not only focus on raising awareness and encouraging preventive actions but also equip individuals with guidance and skills for planning and reserving resources. Households that implement these measures may lessen the adverse impacts of health crises by enabling them to respond promptly until professional health support becomes available.

Global estimates indicate that between 50% and 92% of households are inadequately prepared for general emergencies [14]. In Hong Kong, a mere 3% of households are fully prepared for an influenza outbreak, while 41% exhibit no signs of preparedness actions [15]. There is a noticeable scarcity of data related to household outbreak preparedness in Malaysia. Local studies have noted that flood preparedness among Malaysians is relatively low, with less than half of the general public (44%) being adequately prepared and only 20% being fully prepared. Individuals primarily focus on protecting essential documents, planning for property safety, and locating the nearest evacuation facilities [16]. In contrast, flood preparedness levels in an indigenous community in Pahang are considerably lower, with 30% having property safety measures and only 10% implementing food and life-safety measures [9]. These findings indicate that both the general Malaysian population and marginalized communities exhibit inadequate preparedness levels; however, marginalized communities, especially indigenous groups, are more vulnerable and may experience more serious consequences during outbreaks, particularly with the threat of Disease X [17].

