\begin{document} m = \frac{(Z_{1-\alpha/2} + Z_{1-\beta})^2 \, 2\sigma^2}{\Delta^2} \left[ 1 + (n - 1)\rho \right] \end{document}

where *m* is the number of households per arm; *Z_1−α/2_* is the standard error associated with a 95% confidence interval (*Z_1−α/2_*=1.96); *Z_1−β_* is the standard error associated with 80% power (*Z_1−β_*=0.842); Δ is the mean awareness score difference between the pre- and post-assessments in the intervention group within a community-based trial on disaster preparedness intervention (Δ=15.97) [26]; σ^2^ is the total variation in awareness score between the pre- and post-assessments in the intervention group within the same trial (σ^2^=138.949) [26]; *n* is the estimated median number of households in Proto-Malay majority Orang Asli villages in Selangor (*n*=54) [18]; and ρ is the intracluster correlation coefficient (ICC) (ρ=0.048) [27].

Allowing for an anticipated attrition rate of approximately 30%, the ideal sample size was set at 45 households per arm. Following the CONSORT Statement recommendation that each study arm should include at least four clusters [28], this study employs multistage sampling to select four Orang Asli villages per arm, aiming for 12 households in each village, a total of 96 households for the study.

Eligibility criteria

Table 2 outlines the eligibility criteria for clusters at both the district and village levels. Meanwhile, Table 3 provides the inclusion and exclusion criteria for participants who will represent their households by participating in X-SIAGA and completing a questionnaire designed to assess the change in preparedness scores at all data collection points.

**Table 2 TAB2:** Eligibility criteria for district and village level clusters.

District	Village
Districts in the state of Selangor.	Villages that have not previously participated in any outbreak preparedness programs.
Districts with gazetted Orang Asli villages.	Villages with more than 12 households.
Districts with more than 5 Orang Asli villages.	Villages accessible via road transport.

**Table 3 TAB3:** Inclusion and exclusion criteria of participants.

Inclusion criteria	Exclusion criteria
Orang Asli descent.	Having physical or cognitive disabilities (e.g., blindness, deafness, schizophrenia and dementia).

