Data collection will be conducted by using the Household Outbreak Preparedness Evaluation (HOPE) questionnaire, administered at four intervals: (i) before the intervention (T0); (ii) immediately after the intervention, with the intervention group having received both the X-SIAGA intervention and educational brochures and the control group having received educational brochures only (T1); (iii) at one month post-intervention (T2); and (iv) at three months post-intervention (T3). The HOPE questionnaire is an adapted and translated instrument based on prior studies on household preparedness for outbreaks and general disasters [15,24]. Validation of the HOPE questionnaire will be published elsewhere. The questionnaire is self-administered, with assistance available from trained research assistants and representatives of the village committee if participants require support.

Outcome measures

The scoring for the HOPE questionnaire follows Sumaja’s methods [24]. The primary outcome measure, the Household Outbreak Preparedness score, represents the equally weighted average of the Cognitive Preparedness and Preparedness Behavior scores. By using Sumaja’s preparedness matrix [24], scores will be normalized to a scale of zero to one, and a cut-off value of 0.5 at the x- and y-axes will categorize households’ outbreak preparedness into four groups: Fully Prepared, Committed, Aware, and Unprepared.

Secondary outcome measures include the Cognitive Preparedness and Preparedness Behavior scores. The Cognitive Preparedness score assesses household knowledge, attitudes, and health beliefs, while the Preparedness Behavior score evaluates the skills acquired and practices adopted by households to prepare for potential Disease X and outbreaks.

Control of bias

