To prevent contamination bias, the study ensures sufficient geographical separation between intervention and control villages to minimize interactions among participants from different groups. Prior to recruitment, the research team held meetings with village leaders and committee members, in the presence of JAKOA officials, to explain the X-SIAGA intervention, emphasize the importance of strict confidentiality, and discourage discussions about the intervention. These leaders and committee members then conveyed this information to eligible participants during household recruitment. All participants will again receive a detailed explanation of the privacy and confidentiality policy when expressing interest in joining the trial, and only those who provide consent will be enrolled. To mitigate attrition bias, the study will employ an Intention-to-Treat (ITT) approach. Additionally, to sustain motivation and engagement, perishable goods will be offered as incentives at each stage of data collection.

Statistical methods

The statistical analysis for this study will be carried out by using the IBM SPSS Statistics for Windows, Version 26 (Released 2018; IBM Corp., Armonk, New York). Descriptive statistics will include frequency and percentages for categorical data and mean and standard deviation for numerical data.

To compare baseline sociodemographic characteristics between the intervention and control groups, a Pearson Chi-Square test will be utilized for categorical variables, while an Independent Samples t-test will be used for continuous variables. To evaluate changes over time from T0 to T3 between and within the groups, a repeated-measures analysis of variance will be conducted. To assess variation in results between and within the groups across the different time points, while also controlling for potential confounding variables, a generalized estimating equation will be utilized.

Statistical analyses will use a two-tailed test to evaluate the superiority hypothesis. The null hypothesis states that there is no difference between the X-SIAGA intervention package and standard educational brochures. A significance level of 0.05 will be applied.

Data management

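### The sample size enters a one-arm before-after awareness gain where its formula needs a between-arm difference, so the 80% power does not apply to the primary comparison

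*Protocol article*

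**What the plan says.** The Sample size section of the protocol article takes a formula for two-arm parallel cluster trials, with the usual 2σ²/Δ² term and a design effect. It defines Δ = 15.97 as the "mean awareness score difference between the pre- and post-assessments in the intervention group" of an external trial in disaster preparedness. σ² = 138.949 is described as the variation between the same two assessments in the same arm of that external trial. The remaining inputs are z = 1.96, z = 0.842 ("standard error associated with 80% power"), 54 households per village and an ICC of 0.048. The result is 30 households per arm, raised to 45 for about 30% attrition. The plan is then four villages of 12 households per arm, 96 households in all.

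The trial tests something else. Under Statistical methods, "The null hypothesis states that there is no difference between the X-SIAGA intervention package and standard educational brochures", and "Statistical analyses will use a two-tailed test to evaluate the superiority hypothesis". Under Outcome measures, the primary score "represents the equally weighted average of the Cognitive Preparedness and Preparedness Behavior scores". The article gives no expected between-arm difference, no expected change in the brochure arm and no SD for the primary score.

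**The concern.** The factor 2σ² makes Δ a difference between two independent arms. A gain within one arm equals that difference only if the other arm gains nothing. Nothing has been subtracted here for the control arm, although controls receive brochures on communicable disease prevention and complete the same questionnaire four times. Some control gain is therefore plausible, though the article does not quantify it.

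The construct differs too. Δ and σ describe awareness, while half of the primary score is behaviour. The Introduction says of existing programmes aimed at awareness and transmission risk that "evidence suggests that such approaches do not necessarily translate into tangible preparedness outcomes". A standardised effect seen on awareness need not carry over to the composite.

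The article thus attaches 80% power to a comparison for which no power was calculated. A reader of a null result would not know which between-arm effects the trial could have detected.

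**Working it through.** **1. Reproduce the stated figure.** All inputs are from the Sample size section.

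- Before clustering: (1.96 + 0.842)² × 2 × 138.949 / 15.97² = 7.851 × 277.898 / 255.04 = 8.555
- Design effect: 1 + (54 − 1) × 0.048 = 3.544
- m = 8.555 × 3.544 = 30.3 households per arm, against 30 stated. Rounding up to 31 and dividing by 0.7 gives 44.3, hence the 45 stated.

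The arithmetic is sound. The problem is what Δ and σ² represent.

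**2. Implied effect.** σ = √138.949 = 11.79, so d = 15.97 / 11.79 = 1.355 SD.

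**3. Precision of the planned design.** With k households analysed per village and four villages per arm, in SD units:

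DE = 1 + (k − 1) × 0.048 and SE = √(2 × DE / (4k))

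- k = 12: DE = 1.528, SE = √(2 × 1.528 / 48) = 0.2523
- k = 8.4 (30% attrition): DE = 1.355, SE = √(2 × 1.355 / 33.6) = 0.2840

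Power comes from a non-central t with 8 − 2 = 6 df (critical value 2.447, two-sided 0.05) and non-centrality d/SE. This treats the test as one post-intervention comparison without baseline adjustment.

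**4. Power by assumed control gain.** The control gain is an assumption, shown as a range. Other inputs are as stated.

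| Control gain, share of Δ | Net Δ | Net d | Power, 12 per village | Power after 30% attrition |
|---|---|---|---|---|
| none | 15.97 | 1.355 | 99% | 98% |
| one quarter | 11.98 | 1.016 | 92% | 84% |
| one half | 7.99 | 0.677 | 61% | 52% |
| three quarters | 3.99 | 0.339 | 20% | 17% |

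**5. Detectable difference at 80% power.**

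- 12 per village: 0.850 SD. 0.850 / 1.355 = 63% of the stated effect, so a control gain of up to about 37% of Δ is absorbed.
- After 30% attrition: 0.956 SD. 0.956 / 1.355 = 71%, so up to about 29% is absorbed.
- If district is adjusted for (5 df): 0.887 and 0.998 SD.

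**6. Sensitivity to baseline adjustment.** If adjustment multiplies the variance by 1 − r² (r assumed), power at a one-half control gain rises from 61% to 73% (r = 0.5) or 88% (r = 0.7). After attrition it rises from 52% to 63% or 79%.

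**The case against.** The strongest reply is that the design has a margin the stated calculation hides. Its design effect of 3.544 assumes 54 households per village, while the planned 12 give 1.528. The planned design therefore has 99% power at the stated Δ and tolerates a sizeable control gain. This stands. It limits the consequence but does not turn 15.97 into a between-arm difference.

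A reader might infer that the trial is underpowered, or that realistic effects were never powered. The article does not support that. It does not say which between-arm effect is realistic, and at a one-quarter control gain power is still 92%, or 84% after attrition. Nor can one say that the control arm will certainly move. The Introduction's remark about awareness programmes fits the brochures at least as well as X-SIAGA, and so also hints at little control movement on behaviour.

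Two further replies hold. The 0-1 scaling of the primary score is not a fault in itself, because the formula depends only on Δ/σ; what matters is the change of construct. And the planned repeated-measures and estimating-equation analyses use baseline data, which could raise the power figures above. The article also notes that data on household outbreak preparedness are scarce in Malaysia, which explains the use of a proxy but does not make a one-arm change a between-arm one.

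**Conclusion.** The point holds as a mis-specified target difference. The stated 80% power belongs to a one-arm awareness gain treated as a between-arm effect, and not to X-SIAGA plus brochures against brochures on the preparedness score. Whether actual power is above or below 80% cannot be settled from the article. It is above if the net effect is at least about 63% of the stated Δ (71% after 30% attrition), and 61% or 52% if controls gain half as much.

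These figures assume an ICC of 0.048, eight villages, 6 df, no baseline adjustment, and σ² read as the variance that applies to the between-arm comparison. The last is uncertain, since the article does not say whether 138.949 is a change-score or a single-score variance. Every d derived from it, including 1.355, carries that uncertainty. The detectable differences in SD units do not depend on it.

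**What to change.** Keep 96 households. Stop presenting 15.97 as the target between-arm difference, and restate the section as the difference the planned design can detect for the primary contrast: with 80% power and two-sided 0.05, about 0.85 SD with 12 households per village, or about 0.96 SD after 30% attrition (ICC 0.048, t on 6 df, before any gain from baseline adjustment). Use the planned 12 per village in the design effect. Express the difference on the 0-1 scale once an SD for the primary score is available. If an effect from the literature is kept for context, it should be a control-subtracted one, with the variance identified as change-score or single-score.

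The cost is one rewritten paragraph and no extra participants. The downside is that the stated figure becomes less favourable: the trial would claim 80% power only for a large standardised difference.

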**Figure 2 FIG2:**
[figure not shown]
Conceptual framework. Hypothesis 1 (H1): The intervention changes household preparedness levels, potentially improving their capability to respond to Disease X and potential outbreaks; Hypothesis 2 (H2): The intervention changes cognitive aspects related to preparedness, improving knowledge and attitudes, including health beliefs, towards Disease X and outbreaks; Hypothesis 3 (H3): The intervention changes behavioural aspects related to preparedness, enhancing skills and tangible preparedness practices among households for Disease X and outbreak preparedness.

Study setting and participants

The trial will take place in Orang Asli settlements in Selangor that are gazetted and listed under the Department of Orang Asli Development (JAKOA), focusing on the Orang Asli community members as the study population.

Recruitment

For each selected district, a JAKOA representative is engaged to support the study. The JAKOA representative contacts the village leader of eligible villages to gauge interest in participating. If the village leader expresses interest, an initial meeting is scheduled on a mutually agreed date involving JAKOA, the village leader and committee members, and the research team. During this meeting, the study is explained in detail, and any questions or concerns are addressed. Once the village leader and committee members express their commitment, they are provided with a study information sheet, eligibility criteria, participant expectations, and an ethical information statement.

The study is then promoted by the village leader and committee members to eligible participants. A list of interested and eligible individuals is shared with the research team. The research team prepares a WhatsApp invitation, which is sent to and forwarded by the village leader to the listed participants. Participants who attend the baseline assessment on the agreed date and time are briefed on the study and the consent process. Those who provide written informed consent will complete a baseline assessment and follow their cluster’s assigned intervention. Data collection will commence after participants have signed the informed consent forms.

Sample size

Using the formula for a two-arm parallel-group design in cluster trials [25], the trial requires a minimum sample size of 30 households for each arm. The calculations are as follows:

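### The design effect uses 54 households per village although 12 are recruited, so the stated 30 and 45 per arm are not this design's figures (a conservative error)

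*Protocol article*

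**What the plan says.** The Sample size section (Protocol article, Materials and methods) gives one formula for households per arm: (Z₁₋α/₂ + Z₁₋β)² · 2σ²/Δ² · [1 + (n − 1)ρ]. The quantiles are 1.96 and 0.842, Δ is 15.97, σ² is 138.949 and ρ is 0.048. The cluster-size term n "is the estimated median number of households in Proto-Malay majority Orang Asli villages in Selangor", set at 54.

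From this the section concludes that "the trial requires a minimum sample size of 30 households for each arm". After about 30% attrition, "the ideal sample size was set at 45 households per arm". It then cites a reporting-guideline recommendation of at least four clusters per arm and settles on four villages per arm, "aiming for 12 households in each village, a total of 96 households for the study". The section on sampling, randomization, allocation and blinding repeats the target of 12 households per village. It places two intervention and two control villages in each of two districts.

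**The concern.** The design effect measures how much information is lost because households analysed from one village resemble each other. It depends on how many households per village enter the analysis, not on how many live there. The plan enters a population count (54) and then recruits 12. The two cannot both describe the trial: a cluster of 54 is larger than the whole stated minimum for an arm (30) and larger than the whole planned arm (48). Four villages of 54 would be 216 households per arm.

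This is the trial's only sample-size justification. If its clustering term is wrong, the minimum, the attrition-adjusted target and the 80% power attached to the minimum do not describe eight villages of 12 households. A reader cannot tell what difference the design can detect. If recruitment or retention falls short, 30 per arm would be the wrong benchmark. It would also hide that the number of villages limits this design more than the number of households does.

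**Working it through.** **Inputs (Sample size section).** Quantiles 1.96 and 0.842; Δ = 15.97; σ² = 138.949, so SD = 11.79 and Δ/SD = 1.355; ρ = 0.048; n = 54 in the formula; 12 households per village and four villages per arm in the plan; attrition about 30%. The two-sided 5% level is confirmed under Statistical methods.

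**1. The plan's own figure.**
- Unclustered term: (2.802)² × 2 × 138.949 / 15.97² = 7.851 × 277.898 / 255.041 = 8.555.
- Design effect at n = 54: 1 + 53 × 0.048 = 3.544.
- Product: 8.555 × 3.544 = 30.32.

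This reproduces the stated 30, so the origin of that number is clear.

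**2. The same formula with the planned cluster size.**

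| Households analysed per village | Design effect | Households per arm |
|---|---|---|
| 54 (as printed) | 3.544 | 30.32 |
| 12 (as planned) | 1 + 11 × 0.048 = 1.528 | 13.07, i.e. 14 |
| 8.4 (12 × 0.7 retained) | 1 + 7.4 × 0.048 = 1.355 | 11.59, i.e. 12 |

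With attrition, 14 / 0.7 = 20 per arm. Two adults per household take part, so one could instead count 24 adults as the cluster size with the same ICC. That gives a design effect of 2.104 and 18.0. None of these readings of the actual design returns 30.

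**3. What eight villages of 12 can detect.** The formula uses normal quantiles. A comparison of village means with four villages per arm has 8 − 2 = 6 degrees of freedom, or 5 if district is a factor. The two-sided 5% critical value is then 2.447 or 2.571, not 1.96.

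Let d be the difference in SD units and N the households per arm. The standard error is √(2 × design effect / N), and d is solved from the noncentral t distribution for 80% power.

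| Scenario | Standard error (SD units) | df | Detectable d |
|---|---|---|---|
| N = 48, ICC 0.048 | √(2 × 1.528 / 48) = 0.252 | 6 | 0.85 |
| N = 33.6 (30% lost), ICC 0.048 | √(2 × 1.355 / 33.6) = 0.284 | 6 | 0.96 |
| N = 33.6, ICC 0.048, with district | 0.284 | 5 | 1.00 |
| N = 33.6, ICC 0.10 (assumed, for sensitivity) | √(2 × 1.740 / 33.6) = 0.322 | 6 | 1.08 |

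With normal quantiles the first two rows would read 0.71 and 0.80 SD, so the small number of villages has a visible cost. The printed formula therefore overstates one component (cluster size) and omits another (few clusters).

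**4. Power at the plan's own difference.** At 1.355 SD the noncentral t gives 0.993 with 48 per arm and 0.975 with 33.6 per arm, both on 6 df. These values are only as good as Δ and σ², which are discussed under the objection.

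**The case against.** **The error is harmless for the trial's size.** This stands. Correcting n lowers the requirement from 30 to 14 per arm, while 48 are planned and about 33.6 would remain after 30% attrition. No participant, randomisation step or analysis is affected. A reader might infer from a wrong design effect that the trial is too small, but on the plan's own inputs the documents do not support that.

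**The document already derives 96 from the layout.** This also stands. The Sample size section shows 96 as eight villages of 12 and does not claim that 48 per arm gives exactly 80% power. The 80% belongs to the minimum of 30.

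**The rounding is trivial.** Agreed. A result of 30.32 calls for 31, a difference of one household. A reader might also infer that 45 can only have come from 31 / 0.7 = 44.3, since 30 / 0.7 = 42.9. The text does not show that: the attrition rate is approximate, and 45 is presented as a chosen target.

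**The corrected numbers could mislead in turn.** This is the strongest point. A reader might infer that the trial really has 99% power, or really needs only 14 households per arm. The documents support neither. Δ and σ² describe a pre-post change in awareness score within the intervention group of another trial, not a between-arm difference in the Household Outbreak Preparedness score. The detectable differences in SD units avoid that input. They still assume the cited ICC and an unadjusted comparison at one time point, whereas Statistical methods plans repeated-measures analysis of variance and generalized estimating equations across four assessments.

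**A condensed article may leave sensitivity rows to a fuller document.** Fair as regards their absence, which is not the finding. The finding is that a printed input contradicts the printed design. What survives these objections is the wrong n and the figures that follow from it.

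**Conclusion.** The concern holds in a limited form. The design effect takes the village population median where the number recruited per village belongs, and nothing in the document offers 54 as a deliberate safety margin. The stated 30 and 45 per arm therefore do not follow from this design: its own formula gives 14 per arm, or 20 after 30% attrition. The use of normal quantiles with eight villages is a second, smaller flaw in the opposite direction.

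The net error is conservative on the plan's own inputs, and 96 households are not shown to be too few. The detectable differences of 0.85 to 1.08 SD rest on equal village sizes, the stated or assumed ICC, and an unadjusted village-level comparison at one time point. Severity is moderate: the justification is wrong as written, but enrolment and conduct do not change.

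**What to change.** Rewrite the sample-size paragraph:

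- Set n to 12 households per village, or about 8.4 retained, giving a design effect of 1.528 or 1.355.
- Use t quantiles on 6 degrees of freedom (5 if district is in the model) and round up.
- Withdraw the statements of a minimum of 30 and an ideal of 45 per arm. Keep the existing derivation of 96 as eight villages of 12.
- State what that layout can detect at 80% power: about 0.85 SD with no attrition, 0.96 SD with 30% attrition (1.00 SD on 5 df), and 1.08 SD at an ICC of 0.10 with 30% attrition on 6 df. Mark these as conditional on the ICC and on an unadjusted village-level comparison.
- Do not substitute 14 per arm or 99% power as a validated result, given where Δ and σ² come from.

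The cost is one rewritten paragraph. No additional participants or villages are needed.

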Malaysian citizen.	Having severe health conditions (e.g., respiratory and cardiovascular disease requiring oxygen support such as severe asthma, Chronic Obstructive Pulmonary Disease, heart failure and congenital heart diseases).
Age 18 years old and above.	Residing temporarily (less than 2 years).
The head of the household, or the person who contributes to, or influences health-related decisions for the household.	Intending to relocate to a different village within the next 2 years.
Live in a household with more than two members.	
Able to converse, read and write in Malay.	

Sampling, randomization, allocation, and blinding

The study utilizes a multistage sampling approach with computer-generated randomization for the allocation of villages into the intervention or control arm. Due to potential variability in participant numbers and logistical challenges, simple randomization is employed over block randomization for its flexibility and straightforward, unbiased allocation. The entire sampling, randomization, and allocation process is conducted independently by an external health professional with research experience.

First, two districts in Selangor are randomly selected from the eligible pool. Within each district, four villages are randomly chosen. These villages are then divided, with two randomly allocated to the intervention group and two to the control group in each district (i.e., each district has two intervention villages and two control villages). This approach aims to achieve homogeneous sociodemographic groups among the households. Household recruitment in each village is voluntary, facilitated by JAKOA, village leaders, and committees, targeting 12 households per village.

Given the nature of the intervention, the authors are inevitably aware of group allocation. Procedures are identical for both groups, and research assistants are not provided with information about the study sequence or allocation; hence, they remain uninformed about group assignment. Participants in both groups will remain blinded to their allocation throughout the study.

Intervention

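### The allocation is labelled simple rather than block randomisation, but the procedure is one block of four villages per district, and the statistical methods do not name district

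*Protocol article*

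**What the plan says.** In the protocol article, the section on sampling, randomization, allocation, and blinding describes "computer-generated randomization for the allocation of villages into the intervention or control arm". It then says that "simple randomization is employed over block randomization for its flexibility and straightforward, unbiased allocation", and gives two reasons: uncertain participant numbers and logistics.

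The next paragraph sets out the steps. First, "two districts in Selangor are randomly selected from the eligible pool". Then: "Within each district, four villages are randomly chosen". The four are split evenly between the arms, so that "each district has two intervention villages and two control villages". The stated aim is to make the groups alike in sociodemographic terms. A health professional from outside the team carries out the whole process.

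The sample size section uses multistage sampling to "select four Orang Asli villages per arm, aiming for 12 households in each village, a total of 96 households for the study". The intervention and control sections each refer to four villages.

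The statistical methods section plans two outcome analyses. The first: "To evaluate changes over time from T0 to T3 between and within the groups, a repeated-measures analysis of variance will be conducted". The second is described thus: "while also controlling for potential confounding variables, a generalized estimating equation will be utilized". The confounders are not listed, and neither analysis names district.

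**The concern.** Two adjoining paragraphs name one method and describe another. Under simple randomisation each village is allocated independently, and nothing guarantees an even split. A fixed two-and-two split within district is stratified blocked allocation, which is the method the article says it set aside. One of the two reasons given, uncertain participant numbers, relates to household recruitment; the units allocated are villages, and their number is fixed at eight. The other reason, logistics, could apply to villages, but it does not make the 2:2 rule simple randomisation.

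The label matters for two reasons. The allocation is delegated, so the written instruction should match what is to be done. A final report that repeats the label would also misdescribe how the trial was randomised.

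The analysis follows from this. When allocation is balanced within district, the balance improves precision only if the model accounts for district. With eight villages, the error term has few degrees of freedom, and any between-district variation left in it weighs heavily.

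**Working it through.** **Inputs.** Two districts, four villages per district, two villages per arm in each district, four villages per arm, 12 households per village (sampling and sample size sections).

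**The plan's own figure.** The sample size formula gives (1.96 + 0.842)² × 2 × 138.949 / 15.97² = 8.555. Multiplied by 1 + (54 − 1) × 0.048 = 3.544, this is 30.3 households per arm, against 30 stated. The target is 8 × 12 = 96. None of this depends on the randomisation method, so the point changes no sample size.

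**Number of allocations.**
- Simple randomisation of eight villages: 2⁸ = 256.
- Two of four villages drawn in each of two districts: C(4,2)² = 6² = 36.

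**What simple 1:1 randomisation would give.**
- 2:2 in both districts: (6/16)² = 0.141.
- 4:4 overall: C(8,4)/2⁸ = 70/256 = 0.273.
- At least one district with all four villages in one arm: 1 − (1 − 2/16)² = 0.234.

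The guaranteed 2:2 split therefore cannot come from simple randomisation.

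**Effect of omitting district.** Take eight village means with standard deviation σ, and let one district lie k·σ above the other. With two villages per arm in each district, the shift cancels from the arm difference, whose variance is σ²(1/4 + 1/4) = 0.5σ² for any k. The estimate is unbiased. Without a district term, the residual sum of squares has expectation 6σ² + 8(kσ/2)² on 6 degrees of freedom, so the error variance is overestimated by a factor of 1 + k²/3. That is 1.08 at k = 0.5, 1.33 at k = 1 and 2.33 at k = 2. With a district term the factor is 1, on 5 degrees of freedom (critical t rises from 2.45 to 2.57).

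A simulation of this village-level t-test (40,000 runs, nominal two-sided 5%, assumed arm effect 2.5σ) gives:

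| Assumed district shift k | Type I error, no district term | Power, no district term | Type I error, with term | Power, with term |
|---|---|---|---|---|
| 0 | 5.1% | 84% | 5.0% | 80% |
| 0.5 | 4.3% | 81% | 5.0% | 80% |
| 1 | 2.9% | 75% | 4.9% | 80% |
| 2 | 0.6% | 47% | 5.1% | 80% |

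The values of k and the effect of 2.5σ are assumptions; the article gives neither. The t-test is also not the planned analysis, which is a repeated-measures ANOVA and a GEE. The table isolates what happens when the stratum is ignored. It says nothing about how those two methods handle clustering by village.

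**The case against.** The strongest reply is that the procedure itself is not in doubt. The steps are spelled out, the 2:2 result is restated in brackets, and four villages per arm appears in several sections. Whoever follows those steps cannot end with a 3:1 or 4:0 district. This stands. A reader might infer from the 14.1%, 27.3% and 23.4% figures that the planned balance is likely to fail. The article does not support that inference: the figures show that the label is wrong, not that imbalance is to be expected.

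A second reply is that district is not excluded from the analysis. The GEE adjusts for confounders that are not listed, and a covariate list often sits in a full protocol or analysis plan that is not shown here. This also stands. It would be too strong to say that the analysis leaves district out; the supportable statement is that the statistical methods do not name it. The repeated-measures ANOVA, however, is described by group and time only.

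A third reply is that omitting a balanced factor does no harm to validity. Within this isolated calculation that is right: the estimate is unbiased and the type I error falls below the nominal level. A reader might infer a risk of false positives from omitting district, and the calculation shows the opposite. The harm is lost power. If districts do not differ, there is no such harm, and the unadjusted test is slightly the more powerful (84% against 80%).

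None of these replies rescues the sentence on simple randomisation. It is contrasted explicitly with block randomisation, and drawing two of four villages in each district is a block of four.

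**Conclusion.** The article misnames its allocation method. What it describes is 1:1 allocation within district in one block of four, with 36 possible allocations. The method it names has 256 and would meet the 2:2 rule in both districts 14.1% of the time. This part is exact and needs no assumption beyond equal allocation probability.

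The analysis part is more limited. The methods do not name the stratification factor. If it is omitted, the arm estimate stays unbiased, the test becomes conservative and power is lost. The size of the loss is unknown because between-district variance is not given. Over assumed shifts of 0 to 2 village-mean standard deviations, it ranges from none to a fall from 84% to 47%.

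The sample size is unaffected. The correction is worth making because it concerns how the trial is randomised and costs almost nothing.

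**What to change.** In the section on sampling, randomization, allocation, and blinding, replace the sentence that prefers simple to block randomisation with: *villages are allocated 1:1 within district by a computer-generated permuted block of four (stratified by district)*.

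In the statistical methods section, add: *district is included as a fixed effect in the models comparing the arms on the primary and secondary outcomes*. This should not extend to the baseline chi-square and t-tests. If an analysis plan that is not shown already names district, the article needs only to agree with it.

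The cost is one sentence in each of two sections, with no change to sample size or conduct. The downside is one village-level degree of freedom (6 to 5) and slightly lower power if the districts turn out not to differ.
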